## Abstract

**Background:**

To achieve higher effectiveness in population-based SARS-CoV-2 surveillance and to reliably predict the course of an outbreak, screening, and monitoring of infected individuals without major symptoms (about 40% of the population) will be necessary. While current testing capacities are also used to identify such asymptomatic cases, this rather passive approach is not suitable in generating reliable population-based estimates of the prevalence of asymptomatic carriers to allow any dependable predictions on the course of the pandemic.

**Methods:**

This trial implements a two-factorial, randomized, controlled, multi-arm, prospective, interventional, single-blinded design with cluster sampling and four study arms, each representing a different SARS-CoV-2 testing and surveillance strategy based on individuals’ self-collection of saliva samples which are then sent to and analyzed by a laboratory. The targeted sample size for the trial is 10,000 saliva samples equally allocated to the four study arms (2500 participants per arm). Strategies differ with respect to tested population groups (individuals vs. all household members) and testing approach (without vs. with pre-screening survey). The trial is complemented by an economic evaluation and qualitative assessment of user experiences. Primary outcomes include costs per completely screened person, costs per positive case, positive detection rate, and precision of positive detection rate.

**Discussion:**

Systems for active surveillance of the general population will gain more importance in the context of pandemics and related disease prevention efforts. The pandemic parameters derived from such active surveillance with routine population monitoring therefore not only enable a prospective assessment of the short-term course of a pandemic, but also a more targeted and thus more effective use of local and short-term countermeasures.

**Trial registration:**

ClinicalTrials.gov DRKS00023271. Registered November 30, 2020, with the German Clinical Trials Register (Deutsches Register Klinischer Studien)

## Background

### Study background

In 2020, the novel coronavirus SARS-CoV-2 led to the global spread of the coronavirus disease (COVID-19), which can cause a highly fatal severe acute respiratory syndrome (SARS). In Germany, SARS-CoV-2 infections first occurred in localized hotspots in early spring, but soon spread exponentially to the larger population, with further spread contained by a 2-month-long nationwide lockdown soon after [1]. While effectively containing the virus spread and thus protecting the health of the public, this lockdown also produced long-lasting negative effects within the economic sector by increasing unemployment, bankruptcies, private and public financial debt.

A second SARS-CoV-2 wave reached Germany in fall 2020, characterized by more hotspots than in the first wave, and a fast spread of the virus across different population groups. Although inevitable to ensure disease prevention and functionality of the healthcare system, the discussion of a second nationwide lockdown was faced with strong political and societal criticism, which led initially to milder measures with respect to limiting social encounters when compared to the first wave.

Germany, as most other countries, relies largely on passive monitoring strategies with regard to SARS-CoV-2 surveillance. This usually includes a monitoring focus on those individuals presenting with clinical COVID-19 symptoms and the tracing of contact persons in case of a positive test result. To effectively monitor virus spread and to reliably predict the course of an outbreak, an active surveillance strategy may improve the monitoring and prediction of the spread of an outbreak. These include monitoring of the entire population, hence identifying and observing also asymptomatic SARS-CoV-2 carriers. Such asymptomatic carriers are estimated to represent about 40% of the population during a pandemic and therefore play a key role in uncontrolled infection spread [2, 3].

In contrast to passive surveillance, active routine surveillance further produces more reliable as well as sufficiently dynamic prevalence estimates for both asymptomatic and symptomatic virus carriers within a defined population. Such dynamic prevalence measures are crucial to not only allowing more accurate predictions on the course of a pandemic, but also in providing policy makers with essential information on containment measures that are more locally tailored and overall, less invasive. The World Health Organization therefore recommends that countries perform active surveillance, including testing, isolating cases, and tracing contacts [4]. Further, pooled sample approaches to mass testing might substantially reduce the number of tests required to screen a population and therefore represent a potential active surveillance strategy [5]. However, evidence on the application of such comprehensive, rapid and cost-effective, localized mass testing strategies in a real-world context is currently unavailable.

### Study aims

This trial therefore intends to generate evidence on the effectiveness and cost-effectiveness of different context-specific pooled sample active surveillance strategies. From the perspective of health policy makers, a key aspect of active population surveillance is to identify the most appropriate strategy with respect to its effectiveness and cost-effectiveness in the context of a health system’s defined testing capacity. The aim of the *CoV-Surv Study* is therefore to evaluate four different active surveillance strategies for their respective effectiveness in determining and predicting the prevalence of SARS-CoV-2 infections in a defined population. To also address any economic considerations, the *CoV-Surv Study* also assesses the costs and cost-effectiveness of each of the four strategies, compared to the status quo of passive surveillance. In addition, the *CoV-Surv Study* also includes an additional qualitative component to determine the acceptability of each strategy within the participating population to gain further insight into the overall applicability and user-friendliness of each strategy.

### Related literature

The novel coronavirus SARS-CoV-2 appeared first in Wuhan, China, in December 2019 and was characterized by the clustered occurrence of viral pneumonia cases [6]. Since then, the virus has spread globally with more than 70 million identified cases and more than 1.6 million deaths worldwide [7]. This rapid spread prompted the World Health Organization to declare the initial outbreak a global pandemic on March 11, 2020 [8].

Symptoms of SARS-CoV-2 infection range from fever, headache, and cough to severe shortness of breath with signs of respiratory failure [6, 9]. SARS-CoV-2 shows relatively high transmissibility during the early course of an infection in both symptomatic and asymptomatic patients [2, 10]. Its relatively high human-to-human transmission contributes not only to the pandemic spread but also creates enormous challenges to any monitoring and containment efforts. Until the global availability of effective vaccines, containment of the pandemic will largely depend on efforts preventing transmission and the strengthening of public and clinical health infrastructure [11].

The gold standard for laboratory-based SARS-CoV-2 testing includes the analysis of swabs taken from the upper respiratory tract using real-time reverse transcriptase-polymerase chain reaction (RT-PCR), a technology used to detect viral RNA [12]. This RT-PCR test is highly sensitive in detecting SARS-CoV-2 RNA during an acute infection [12]. Presently, the cost of an RT-PCR test ranges between € 25 and 40 (cost of sample collection not included), which would make an active monitoring strategy with routine laboratory-based mass testing of respiratory samples only feasible if relying on pooled testing [5].

With respect to mass testing, the collection of nasopharyngeal or oropharyngeal swabs by medically trained personnel, the required infection protection measures would pose an additional logistical challenge. A more feasible alternative sampling strategy is therefore to have individuals obtain their own swabs and sent them to the laboratory or testing site. There is also increasing evidence that simple saliva, sputum, or throat samples produced from gargling are suitable testing materials with respect to sensitive SRAS-CoV-2 detection [13–16]. Furthermore, tests based on reverse transcriptase loop-mediated isothermal RNA amplification (RT-LAMP) assays represent suitable alternatives to RT-PCR and could further reduce the cost of viral RNA testing of alternative sample materials [17, 18].

### Significance of study

Findings of the *CoV-Surv Study* will inform the choice of the most effective, acceptable, and cost-effective strategy for SARS-CoV-2 screening and testing, with the most effective and cost-effective strategy expected to be incorporated into the local public health department’s routine health surveillance activities. Additional investigation of its everyday performance will provide insight in the strategy’s applicability to real-time prevalence prediction and the usefulness of the resulting information for local policy makers to implement countermeasures to effectively prevent future nationwide lockdowns.

## Methods/design

### Study outcomes

Identification of the one best strategy will be determined by a series of parameters. Primary study outcomes include cost per correctly screened person (including costs related to contacting, pre-screening, and testing of participants); cost per positive symptomatic and asymptomatic case (including costs related to contacting, pre-screening, and testing of participants); positive detection rates (i.e., 4-week cumulative SARS-CoV-2 prevalence); and the precision of positive detection rates (i.e., confidence intervals of the estimators).

Further, secondary outcomes include the overall participation rate (i.e., number of participants for whom a test result—with and without pre-screening—is available out of the total number of contacted participants), costs per asymptomatic case, prevalence estimates, number of asymptomatic cases by strategy, ratio of symptomatic to asymptomatic cases by strategy, and participant satisfaction.

Lastly, the *CoV-Surv Study* includes additional study components, i.e., a cost-effectiveness analysis, a prognostic modeling, and a qualitative assessment of participant perception and experience, which will complement trial data with data from other sources to address the following tertiary outcomes: cost-effectiveness of each of the four active strategies compared to the status quo of passive surveillance, the development of a prognostic model to predict hospital utilization caused by SARS-CoV-2, time between test shipment and test application, and time between test shipment and test result, as well as the perception and preferences of persons in respect to being subjected to surveillance.

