#### Strategy A1

Individuals (one per household) receive information and study material by mail with instructions on how to produce a saliva sample and how to return the sample by mail. Once received by the laboratory, the sample is tested for SARS-CoV-2 using RT-LAMP.

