#### Strategy B2

Individuals (one per household) receive information by mail on how to complete a brief pre-screening questionnaire which asks about COVID-19-related clinical symptoms. Only individuals whose pre-screening score crosses a defined threshold will then receive additional study material by mail with instructions on how to produce their own as well as saliva samples from each household member and how to return these samples by mail. Once received by the laboratory, the samples are tested for SARS-CoV-2 using RT-LAMP.

Of the four surveillance strategies, strategy A1 is considered the gold standard for prevalence estimation and thus used to determine the bias introduced by each of the other strategies. To determine the cost-effectiveness, each strategy is compared to a status quo, defined as the currently practiced passive surveillance approach. In each strategy, RT-LAMP-positive samples are additionally analyzed with real-time quantitative RT-PCR (RT-qPCR) in order to minimize the number of false positives.

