### Study materials

Participants are asked to provide a saliva sample in a testing tube after gargling with 5ml saline solution. This sample is shipped to the laboratory by mail and then analyzed for SARS-CoV-2 using the RT-LAMP test. All positive-tested samples undergo additional confirmation analysis using the RT-PCR test. Depending on the strategy, some participants first take part in an online pre-screening survey. This short survey contains between 10 and 15 questions assessing the presence of symptoms of an early SARS-CoV-2 infection. This survey also collects information on a participant’s socio-demographic background (i.e., education, employment, household size). Participants of the qualitative study component further take part in a qualitative survey or an interview with open-ended questions. Participation in this qualitative study will commence after an individual’s trial participation has been completed.

To estimate the cost of the four surveillance strategies, an activity-based micro-costing approach is used to prospectively estimate the average cost per case completely screened and per case detected for each strategy. Data on the resource consumption of all activities related to the implementation of the four strategies will be categorized as either start-up or implementation cost. For each activity, data on resource consumption for both capital cost items (e.g., building, equipment, and vehicles) and recurrent cost items (e.g., personnel, materials, and consumables) will be collected directly from respective trial records. Unit costs will be taken from secondary data sources, such as financial statements, invoices, and salary schedules.

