### Randomization process

The total study sample consists of 10,000 participants with each strategy enrolling 2500 randomly selected participants. Participants are identified and sampled by each selected municipality’s population register provided by the respective registration office. Individuals or households are drawn as a stratified sample proportional to population size. For each of two strata (i.e., all municipalities located in the “Rhein-Neckar District” or in the municipality of the city of “Heidelberg”), individuals or households are drawn in three batches of each three continuous weeks.

For the “Rhein-Neckar District” stratum, a two-stage sample design is used for each batch, within which the primary sampling units (PSU) are drawn as synthetic clusters of secondary sampling units (SSU) (i.e., individuals or households). First, 55 PSUs are randomly selected for each batch independently using probability proportional to size sampling. These 55 PSUs are then distributed across the 56 municipalities (i.e., sampling points) in the “Rhein-Neckar District” stratum using the Cox algorithm. This might result in some sampling points to contain several PSUs. Second, disproportional sampling is used to draw the same number of SSUs for each sampled PSU in order to obtain a self-weighted sample of individuals or households [19]. Since sampling points can contain several PSUs, the number of SSUs per sampling point and batch may vary. As the “Heidelberg” stratum consists only of one municipality, selection of individuals or households is carried out in a single-step simple random sampling process.

The net sample size is then translated into a corresponding gross sample under consideration of the expected response rates in each strategy and the sensitivity and specificity of the pre-screening tool applied to strategies B1 and B2 (see below). The gross sample therefore includes a total of 21,739 individuals or households contacted in the “Rhein-Neckar District” and 6386 in the “Heidelberg” stratum. This way a sample of 28,125 individuals or households is drawn and then randomly allocated to the four strategies A1, A2, B1, and B2 in the ratio 5 to 2.5 to 14 to 7 to eventually yield a final study sample of 2500 saliva tests for each strategy.

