### Power calculation

Based on a dynamic Bayesian prevalence estimate, the successful surveillance strategy is expected to test up to 1000 saliva samples per day in order to generate 2- to 5-week predictions on critical care capacity and other relevant health care parameters in the Rhein-Neckar [22]. Each studied strategy should therefore be able to estimate SARS-CoV-2 prevalence with sufficient accuracy. In May 2020, the 4-week cumulative SARS-CoV-2 prevalence estimated by passive monitoring in the Rhein-Neckar District was around 0.25%. Assuming an equally high prevalence of asymptomatic SARS-CoV-2 carriers, the overall prevalence of asymptomatic and symptomatic carriers was approximately 0.5%. A similar prevalence is assumed for future waves.

Strategy A1 is designed to directly reflect the pandemic events using a purely random sample. With a total of 2500 saliva samples, this strategy is able to detect an overall SARS-CoV-2 prevalence of 0.5% with an accuracy of ±0.35% and a power of 95%; a prevalence of 0.2% would be detected with an accuracy of ±0.25% and a power of 93% (confidence interval according to Agresti-Coull) [23]. Assuming a higher SARS-CoV-2 prevalence within families or households of an infected individual, strategy A2 is expected to detect this higher rate accordingly. Given the upstream pre-screening mechanisms and resulting filter effects in strategies B1 and B2, the resulting detection rates related to these strategies should also differ accordingly.

Sample sizes are therefore designed to yield 2500 saliva samples available for analysis in each study arm. The catchment area of the study (i.e., Rhein-Neckar District plus Heidelberg) has approximately 700,000 inhabitants. To ensure sufficient precision of the measured estimates, a total net case number of 1.4% of the target population (i.e., 0.35% per study arm) is targeted. Based on assumptions on participation rates as well as the sensitivity and specificity of the pre-screening tool, the following gross sample sizes are needed for each strategy:

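### The primary positive detection rate is labelled 4-week cumulative prevalence, but one saliva RNA test per person measures positivity at sampling, and the planning prevalence has the same mismatch

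*Protocol article*

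**What the plan says.** Study outcomes, in the protocol article, gives as one primary outcome "positive detection rates (i.e., 4-week cumulative SARS-CoV-2 prevalence", and makes the precision of that rate a further primary outcome.

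The measurement is described in three places. Study materials: "Participants are asked to provide a saliva sample in a testing tube after gargling with 5ml saline solution". Strategy A1: "Once received by the laboratory, the sample is tested for SARS-CoV-2 using RT-LAMP". The closing paragraph of Strategy B2, on all arms: "RT-LAMP-positive samples are additionally analyzed with real-time quantitative RT-PCR". That paragraph also makes A1 the reference for prevalence and for the bias of the other arms. Related literature says of the confirmatory technology: "This RT-PCR test is highly sensitive in detecting SARS-CoV-2 RNA during an acute infection".

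Power calculation starts from this figure: "In May 2020, the 4-week cumulative SARS-CoV-2 prevalence estimated by passive monitoring in the Rhein-Neckar District was around 0.25" percent. It assumes as many asymptomatic carriers again, arrives at 0.5%, and states that 2500 A1 samples give ±0.35% with 95% power at that prevalence. A second scenario, 0.2%, is given ±0.25% with 93% power. On timing, Randomization process says that "individuals or households are drawn in three batches of each three continuous weeks".

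**The concern.** A single RNA test shows whether viral RNA is detectable on the day of sampling. The share positive is therefore a point prevalence, averaged over the days on which samples were taken. A 4-week cumulative figure counts everyone who became a case at any time in four weeks. Collecting single samples over several weeks does not turn the first quantity into the second, because nobody is followed through the window.

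The same step occurs in planning, where a cumulative figure from passive notification becomes a per-sample probability without a conversion. The two scales differ by a factor that depends on how long infected people remain detectable, and the article does not give that duration.

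At stake is what prevalence the trial can claim to have estimated in A1, its reference arm, and how many cases it should expect there. If the results were later read as 4-week cumulative, in the prognostic model or beside notification data, they would be on the wrong scale.

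**Working it through.** **1. The plan's own figures.** Inputs from Power calculation: n = 2500; prevalence 0.5% and 0.2%; accuracy ±0.35% and ±0.25%; Agresti-Coull interval. The confidence level is not stated; 95% two-sided is assumed (z = 1.96).

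With x positives, ñ = n + z², p̃ = (x + z²/2)/ñ, and half-width = z·√(p̃(1 − p̃)/ñ).

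- The half-width is at most 0.35% when x ≤ 18. With X ~ Bin(2500, 0.005), P(X ≤ 18) = 0.949 (stated 95%).
- The half-width is at most 0.25% when x ≤ 8. With X ~ Bin(2500, 0.002), P(X ≤ 8) = 0.932 (stated 93%).

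Both reproduce, so the arithmetic is right. It also shows that 0.5% is used as the probability that one sample is positive, which implies 2500 × 0.005 = 12.5 positives. The article itself states no count.

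**2. Relation between the two scales.** With constant incidence of r per day and a mean detectable period of D days, 4-week cumulative C = 28r and point prevalence P = rD, so P = C × D/28. They agree only when the mean detectable period is 28 days. D is an assumption here, shown as a range.

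**3. A1 with C = 0.5%, n = 2500.**

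| D (days) | P = 0.5% × D/28 | Expected positives | Half-width at that count | Half-width / P | P(no positives) |
|---|---|---|---|---|---|
| 7 | 0.125% | 3.1 | 0.18% | 141% | 4.4% |
| 10 | 0.179% | 4.5 | 0.20% | 111% | 1.2% |
| 14 | 0.25% | 6.3 | 0.22% | 89% | 0.2% |
| 21 | 0.375% | 9.4 | 0.26% | 70% | <0.1% |
| 28 | 0.5% | 12.5 | 0.30% | 59% | <0.1% |

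The probability that the half-width is within ±0.35% is at least 0.996 for every D up to 21 days, because the interval narrows as prevalence falls. The absolute target is met; the relative width grows.

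**4. The 0.2% scenario.** It corresponds to D = 28 × 0.2/0.5 = 11.2 days, so it lies inside the range above, though the article does not present it as a change of scale.

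**5. Gross sample.** With sensitivity 90% and specificity 70%, the screen-positive share is 0.9P + 0.3(1 − P). At P = 0.5% this is 0.303, and 3125/0.303 = 10,313, as stated. At P = 0.125% it is 0.30075, and 3125/0.30075 = 10,391. Dividing each by 0.75 (50%, plus 50% of the remainder after prompting) gives about 13,751 and 13,854 addresses, a change of under 1%.

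**The case against.** The strongest reply is that only a parenthetical gloss is wrong. The positive detection rate and its interval can be computed from the data collected, all arms use the same assay, and contrasts with A1 do not depend on the label. This stands: a reader might infer that the outcome cannot be estimated at all, or that the arm comparisons are distorted, and the documents support neither. The gloss is nevertheless the definition of a primary outcome, and it names a quantity that the design does not measure.

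A reader might also infer that A1's expected positives are overstated as a matter of fact. The documents do not establish that. It needs a mean detectable period below 28 days, roughly constant incidence, and no passive under-ascertainment beyond the assumed doubling. Related literature says that the test is sensitive in acute infection; it does not say that RNA is detectable only then, and gives no duration. The Background describes a fast-spreading second wave, and recruitment ran from November 18 to December 22, 2020, so constant incidence is a simplification. Longer shedding, changing incidence or more missed cases could offset or reverse the difference.

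Nor is the stated precision invalid. The plan promises an absolute half-width, not a relative one, and its 0.2% scenario already covers part of the lower range.

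Finally, Statistical analyses brings in passive surveillance through the number of cases detected, not through 4-week prevalences, so a misleading prevalence comparison is a risk to guard against and not something the article plans. The batches describe when addresses are drawn. They do not supply a 4-week window, but they should not be read as a contradictory analysis window either.

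**Conclusion.** The point holds for the definition and for the planning input. As written, the primary outcome is a 4-week cumulative prevalence, while the measurement is RNA positivity on one occasion. That conclusion rests on the document alone. The 0.5% used for A1 is a doubled 4-week cumulative figure treated as single-sample positivity with no stated conversion.

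The size is conditional. With constant incidence and an assumed mean detectable period of 7 to 21 days, A1 would expect 3.1 to 9.4 positives instead of the implied 12.5, and the half-width would be 141% to 70% of the prevalence instead of 59%. The stated accuracy and power stand, and the gross sample is practically unchanged. The consequence is limited to what prevalence the trial can claim, how many cases it should expect, and how its figures are set beside cumulative ones.

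**What to change.** - **Outcome.** Redefine the primary outcome as the prevalence of confirmed SARS-CoV-2 RNA positivity at sampling, averaged over the sampling period, overall and by batch. If a 4-week cumulative figure is wanted, specify the model that derives it and its assumptions.
- **Planning.** Say that 0.5% is a cumulative figure, state the assumed mean detectable period, and give A1's absolute and relative precision over a range of planning prevalences, for example 0.125 to 0.5%.
- **Comparisons.** Wherever active and passive figures are compared, put both on one scale, for instance passive incidence per day multiplied by detectable days, with a sensitivity range for that duration.

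The cost is wording, one sensitivity table and a less favourable relative precision. No extra participants or samples are needed.
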